From the policy perspective, the decision to use a live-attenuated vaccine prior to a pandemic would be partially influenced by characteristics of the vaccine strain and concerns for reassortment with circulating influenza strains. Such a reassortment event would be particularly concerning for an A/H5N1 strain, for example, which has a demonstrated high case-fatality rate, but is not yet circulating widely and has not acquired the ability to transmit efficiently from person-to-person. Thus, it is important to understand the characteristics of potential pandemic vaccines based on avian strains, to understand their immunogenicity and reactogenicity in humans, and to understand their shedding characteristics, the latter of which could influence their propensity to reassort with circulating human strains.

LAIVs have been used for seasonal influenza vaccines for over 40 years in Russia. The Institute of Experimental Medicine (IEM) in St. Petersburg has been collaborating with PATH Vaccine Solutions (PVS), a nonprofit corporation that is a supporting organization of the nongovernmental global health organization, PATH, to develop prototype live-attenuated cold-adapted reassortant pandemic influenza vaccines based on avian strains. The overall plan includes the generation of a set of live-attenuated cold-adapted reassortant viruses bearing an H5N1 and H7N3 on the attenuated A/Leningrad/134/17/57 (H2N2) master donor strain background. The cold-adapted, live monovalent A/17/mallard/Netherlands/00/95 (H7N3) influenza vaccine will be tested in this study. The virus strain in this vaccine was constructed in the laboratories of IEM by classical reassortment of

A/mallard/Netherlands/12/00(H7N3) virus with a cold-adapted temperature sensitive A/Leningrad/134/17/57(H2N2) virus master strain in developing chicken embryos. The 6:2 genomic reassortant was characterized for acceptable phenotype and genotype [presence of cold-adapted, temperature sensitive, hemagglutinin (HA), and neuraminidase (NA) markers], with genetic sequencing used to confirm the molecular basis of the attenuated phenotype. The developed vaccine strain was transferred to Microgen to produce a bulk lot of vaccine for use in preclinical immunogenicity and challenge studies and for use in clinical trials. Additional information on the development and preclinical testing of this candidate vaccine may be found in the Confidential Investigator's Brochure.

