In order to maintain isolation unit staff blinding throughout the study, one designated investigator will receive all daily results of rRT-PCR testing. This investigator will maintain these results in a secure location and will not share results with other investigators or study staff. Likewise, laboratory personnel conducting the rRT-PCR testing will not share the results with others not designated to receive these results. Only in the event that a subject prematurely leaves the isolation unit for any reason may any subject's influenza A positivity be revealed. The designated person holding these results will not participate in study evaluations of safety. This designated person will be consulted on Day 7 and Day 35 in order to confirm that no subject has influenza A positivity in a nasal swab specimen collected in either of the final two days of planned stay in the isolation unit after each dose.

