### **7.2.1 Day of First Admission into the Isolation Unit (Day 0)**

1. For eligible subjects, a study clinician will review the procedures for the vaccination study and admittance into the isolation unit. A vaccine study ICF (ICF B) should be completed at this time and the subject admitted into the isolation unit. Upon admittance into the isolation unit, a subject may proceed to undergo procedures related to administration of study vaccine or placebo and evaluation of vaccine safety and immunogenicity.
2. At least two hours prior to administration of study vaccine or placebo, a nasal swab specimen should be collected, followed one hour later by collection of a nasal wick specimen. Specimen collection information must be documented on the CRF and in specimen collection logs. Nasal wick specimens will be sent to IEM for mucosal anti-influenza IgA testing.
3. Prior to administration of study vaccine or placebo, a serum specimen will be collected for anti-influenza serologic assays. A whole blood specimen for isolating PBMCs for assessing cellular immune responses will also be collected at this time. Blood specimens will also be collected for testing a CMP and a CBC with differential. Specimen collection information must be documented on the CRF and in specimen collection logs. CMP and CBC with differential test results from specimens collected on Day 0 need not be obtained and reviewed prior to administration of study vaccine or placebo; these results will only served to define baseline status for subjects.
4. The subject will be administered one dose of study vaccine or placebo. Administration of study vaccine or placebo must occur at least one hour after collection of any nasal swab or nasal wick specimens from the subject.
5. The subject will be observed for two hours after administration in case of any immediate reactions. If the subject experiences an immediate adverse reaction, he/she will be treated and the event will be recorded on the CRF.
6. The subject will be observed throughout the day and any AEs that occur will be recorded in the appropriate section(s) of the CRF.
7. At least 6 hours after administration of study vaccine or placebo, a nasal swab specimen will be collected. Specimen collection information must be documented on the CRF and in specimen collection logs.

---

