**7.2.17 Seventh Day after Administration of Dose Two (Day 35)**

1. In the morning between 09:00 and 10:00, a nasal swab specimen will be collected. Specimen collection information must be documented on the CRF and in specimen collection logs. Nasal swab specimens should be tested at RII by rRT-PCR for influenza A positivity on this day with results reported back to one designated investigator by 16:00.
2. Once in the morning and once in the afternoon, study staff will interview the subject about any signs and symptoms the subject might be experiencing. Subjects will be encouraged to spontaneously report any concern or symptom they are experiencing. Any AEs that have occurred will be recorded in the appropriate section(s) of the CRF.
3. A study clinician will perform one scheduled physical examination and record the information on the CRF. Results will be reviewed by study staff and with the subject. Any AEs that have occurred will be recorded in the appropriate section(s) of the CRF and may necessitate additional exams throughout the day.
4. A study otolaryngologist will perform an ENT examination and record the information on the CRF. Results will be reviewed by study staff and with the subject and any AEs that have occurred will be recorded in the appropriate section(s) of the CRF.
5. Blood specimens will be collected for testing a CMP and a CBC with differential. Specimen collection information must be documented on the CRF and in specimen collection logs. Any out-of-normal-range result will be recorded as an AE.

6. A urine specimen will be collected for urinalysis testing via dipstick. Specimen collection information must be documented on the CRF and in specimen collection logs. Any out-of-normal-range result will be recorded as an AE.
7. Subjects will be given a second diary card in which they will be asked to record any local and/or systemic reactions that might appear from days 35 (after discharge from the isolation unit) to 56 and to record any concomitant medications. Subjects will be instructed how to use the second diary card on this day. All relevant explanations should be included in the second diary card. The second diary card will also have contact information for the investigators, should the subject have any questions.

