#### 8.2.2 Special Assays

***Procedures for all laboratory assays will be specified in detailed protocols maintained at the either RII or IEM.***

##### 8.2.2.1 Detection of Shed Virus by rRTPCR

Nasal swab (and conjunctival) swab specimens will be tested for evidence of influenza virus using rRTPCR. These assays will be conducted by RII.

Nasal swab specimen collection for this purpose will occur daily on Days 0-7 and Days 28-35, while a subject is admitted to the isolation unit. Collection must occur both prior to and at least 6 hours after administration of study vaccine or placebo on Days 0 and 28. For nasal swabs collected on Days 1-6 and Days 29-34, results (influenza A positive or negative) of testing for a subject must be complete and determinant within 30 hours of specimen

collection. For nasal swabs collected on Day 7 and Day 28, results (influenza A positive or negative) of testing for a subject must be complete and determinant by 16:00 on that day. Confirmation of subtype should occur within 72 hours of specimen collection.

Conjunctival swab specimen collection will occur only for those subjects who develop conjunctivitis. Conjunctival swab specimens will be collected only on the first day of appearance of conjunctivitis. Results (influenza A positive or negative) of testing for a subject must be complete and determinant within 30 hours of specimen collection. Confirmation of subtype should occur within 72 hours of specimen collection.

Nasal swab specimens collection for rRTPCR testing will only occur past Day 7 or past Day 28 if a subject is requested to remain admitted to the isolation unit because a nasal (or conjunctival) swab specimen was influenza A positive during the final two planned days of stay in the isolation unit after each dose (Days 6 or 7 or Days 34 or 35).

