#### **Virological assays**

Collection of nasal swab specimens will be performed with sterile dry applicators (COPAN Diagnostics, Inc.) using standard procedure in accordance with MG 4.2.2136-06. Following

collection of the material the applicator will be placed into the sterile tube containing transport medium (COPAN).

Virus isolation will be performed in accordance with the WHO manual on animal influenza, 2002). Normally developing 10-11-day-old chicken embryos (Bred Livestock Farm Ltd. "Nasia", Leningrad Region) will be used. Embryos will be inoculated through allantoic cavity route (each specimen applied for 3 embryos) and incubated for 3 days at temperature 32-34°C. The HA positive allantoic fluid with 1% chicken erythrocytes will be further used for typing and sequencing of the virus isolate obtained. In case of negative HA results, blind passage will be performed (3 days incubation at temperature 32- 34°C). When getting negative results the second blind passage will be performed and after that the sample will be evaluated as negative.

Testing of clinical specimens (nasal and conjunctival swabs) will be done by real-time RT-PCR (Rotor-Gene 6000, Australia) using AmpliSense reagent kit for influenza A virus DNA amplification, and by real-time PCR with hybridization fluorescent detection - INFLUENZA Test-System for PCR Detection and Differentiation of Avian Influenza Virus (the Federal Central Research Institute of Epidemiology under Ministry of Public Health of Russia), for identification of influenza A virus H5, H7 and H9 subtypes in biological material.

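### The Day 0 pre-dose influenza A swab has no result-reporting time, and the masking rule withholds a positive from the unit's clinicians although it reveals nothing about allocation

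*Protocol*

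**What the plan says.** Swabs on dosing days: Section 8.2.2.1 states "Collection must occur both prior to and at least 6 hours after administration of study vaccine or placebo on Days 0 and 28". Section 7.2.1 gives the Day 0 order: "At least two hours prior to administration of study vaccine or placebo, a nasal swab specimen should be collected".

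Result times: Section 8.2.2.1 says "For nasal swabs collected on Days 1-6 and Days 29-34, results (influenza A positive or negative) of testing for a subject must be complete" within 30 hours of collection. It then says "For nasal swabs collected on Day 7 and Day 28, results (influenza A positive or negative) of testing for a subject must be complete" by 16:00 that day, and asks for subtype confirmation within 72 hours. Section 7.2.2 gives a reporting time for the Day 1 swab; Section 7.2.1 gives none for Day 0. Section 8.2.3.3 adds that swabs tested by rRT-PCR should be tested within 30 hours, with no day excepted.

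Disclosure: under Sections 5.3.2 and 8.2.2.1 one designated investigator holds all rRT-PCR results and takes no part in safety evaluation. The stated purpose is to keep isolation unit staff blinded. Only on premature exit from the unit "may any subject's influenza A positivity be revealed". The holder is consulted on Days 7 and 35, and only about the last swabs before planned discharge.

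Causality: Section 9.2.2 requires every adverse event to be called related or not related. Section 11.3.1 tabulates events by that judgement, made by a blinded clinician.

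**The concern.** The Day 0 pre-dose swab is the only planned virological test for influenza before the first dose of a live avian-reassortant vaccine. A positive means influenza A acquired outside the study. The protocol treats such infection as important: Section 2.1 cites "concerns for reassortment with circulating influenza strains", Section 2.3.1.1 discusses transmission inside the unit, and Sections 5.5.2 and 9.5 list early seasonal circulation as a ground for suspension.

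Yet as written the result has no reporting time and may not be passed to the clinicians who look after the subject. Fever, cough, sore throat and runny nose are among the solicited signs in Section 9.2.1.2, and wild-type influenza can produce the same picture. A clinician who does not know of the infection may call those events vaccine-related.

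**Working it through.** The plan states no figure on this point, and Section 11.1 says no sample size was calculated. The check is a comparison of passages with some supporting arithmetic.

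**1. Collection days against reporting times in Section 8.2.2.1.**
- Collected: Days 0–7 and 28–35.
- Given a result time: Days 1–6 and 29–34 (30 h); Days 7 and 28 (16:00).
- Left out: Days 0 and 35.

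Day 35 is covered elsewhere. Section 7.2.17 says "Nasal swab specimens should be tested at RII by rRT-PCR for influenza A positivity on this day with results reported back" by 16:00. Day 0 has only the 30-hour testing time in Section 8.2.3.3, which is not a reporting time.

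**2. The Day 28 entry.** Subjects arrive at 08:00 (Section 7.2.10). The earliest post-dose swab is 08:00 + 2 h + 6 h = 16:00, so a 16:00 result is impossible for it. With Section 7.2.17, this suggests that Day 28 in Section 8.2.2.1 is a slip for Day 35. If it is simply replaced, the Day 28 pre-dose swab loses its listed time too.

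**3. Timing against the dose.** The dose may follow the swab by as little as 2 h. A test completed at the 30-hour limit can therefore come 30 − 2 = 28 h after the dose. The general testing time does not put the result ahead of dosing, and no other sentence does.

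**4. Does the Day 0 positive unmask?** It is collected before any study product is given, and Section 5.2 excludes earlier participants in H5 or H7 vaccine trials. Allocation is random, so a baseline result is independent of it. Releasing it tells the clinician nothing about treatment.

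**5. How often it might arise.** Chance of at least one positive = 1 − (1 − p)^n, where p is the prevalence of silent influenza A on Day 0. The protocol gives no p; the values below are assumptions. The vaccine arm is 9 + 21 = 30 and placebo 3 + 7 = 10 (Section 4).

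| p | n = 40 (all Day 0 swabs) | n = 30 (vaccinees) |
|---|---|---|
| 0.25% | 10% | 7% |
| 0.5% | 18% | 14% |
| 1% | 33% | 26% |

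**6. Effect of one case.** One vaccinee wrongly placed in the related column is 1/30 = 3.3% (exact 95% CI 0.1% to 17.2%), against 0/30 (0% to 11.6%).

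**The case against.** Much can be said for the plan as it stands.

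- **Testing time.** A reader might infer that the swab has no time limit at all. Section 8.2.3.3 sets 30 hours for all such swabs, and subtype confirmation is due within 72 hours. The gap is a missing Day 0 reporting time in Section 8.2.2.1.
- **Who knows.** A reader might infer that the result is hidden from everyone. The designated investigator holds it, the Safety Monitoring Committee reviews shedding data for all subjects (Section 4), and shedding is to be reported for every subject and time-point (Section 3.2.2). But the committee meets on or soon after Days 8 and 36, when the daily assessments for that dose have already been made.
- **Screening.** Acute respiratory illness within two weeks and other acute illness are exclusions (Section 5.2), and subjects are examined on Day 0 before dosing (Section 7.1.2). Only subclinical or incubating infection remains.
- **Primary outcome.** A reader might infer that the primary reaction rates would be misattributed. They count events whatever their judged cause, and Section 9.2.2 says relatedness does not decide what is recorded. Only the related/not-related tabulation is exposed.
- **Post-dose positives.** A reader might want every influenza A positive not typed as H7 released as well. That could weaken masking. Vaccinees may shed H7, so a non-H7 positive after dosing may point towards placebo. The influenza A test and the kit "for identification of influenza A virus H5, H7 and H9 subtypes in biological material" are also separate, and nothing shows that every vaccine-virus positive will type as H7.

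These points all stand. They narrow the concern, but none explains why a pre-dose Day 0 positive should be withheld.

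**Conclusion.** The point holds in a limited form. The non-disclosure rule is wider than its blinding purpose: followed literally, it withholds a Day 0 pre-dose positive from the clinicians who treat the subject and judge causality, with no gain in masking. Section 8.2.2.1 also gives that swab no reporting time.

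The size is modest. The chance that it arises at all is about 10% to 33% over the 40 Day 0 swabs for assumed prevalences of 0.25% to 1%, and 7% to 26% among the 30 vaccinees. Counting all 80 pre-dose swabs would give larger figures, but the argument about allocation is certain only for Day 0, since the Day 28 swab follows a first dose. One case could shift a related-event percentage in the vaccine arm by 3.3 points; the primary proportions would not change. The calculation assumes independent subjects, a perfectly accurate assay and the stated prevalences, none of which the protocol supplies.

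**What to change.** - **Section 8.2.2.1:** add a result-reporting time for the Day 0 pre-dose swab. Reconcile the 16:00 entry for Day 28 with the Day 35 rule in Section 7.2.17, and make sure that the Day 28 pre-dose swab still has a stated time afterwards.
- **Sections 5.3.2 and 8.2.2.1:** exempt Day 0 pre-dose influenza A positives, and only those, from the non-disclosure rule, and name the study physician as recipient. Leave the rule unchanged for all post-dose swabs.
- **Safety listings:** flag subjects with a Day 0 pre-dose positive.

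What follows clinically from such a result, and whether it should be tied to dosing, is for the sponsor and the investigator to set.

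The cost is a few sentences and one flag. The swab and the test are already planned, and no masking is lost.

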Subject screening for eligibility will continue and be completed on the second screening day (S2). This second screening day will occur the same day as scheduled admission to the isolation unit and administration of study vaccine or placebo (Day 0). Women will undergo pregnancy tests using urine samples. All subjects will undergo an ear, nose and throat (ENT) examination. Fully eligible subjects will be admitted to the isolation unit. At that time, nasal swab, nasal wick, and blood specimens will be collected for virologic and immunological testing prior to administration of study vaccine or placebo. Blood and urine specimens will be again collected for routine biochemical and hematological blood tests and urinalysis by dipstick; these results will serve to define baseline status for subject prior to receipt of study vaccine or placebo but will not be used for screening purposes. Subjects and investigators conducting assessments of safety will be unaware of which allocation, LAIV H7N3 or matched placebo, is received; study vaccine and placebo will be masked. Subjects will be carefully monitored for adverse reactions while in the isolation unit.

All subjects will remain in the isolation unit for at least 7 days after receipt of study vaccine or placebo. Nasal swabs will be collected daily while subjects are in isolation to test for

**Description of Study  
Design, cont.:**

presence of influenza virus shed in the nasal passage. Any subject exhibiting conjunctivitis will also have a conjunctival swab collected on the day of appearance of the sign. Any subject exhibiting influenza A virus shedding, as determined by real-time RT-PCR positivity on a nasal swab specimen, in the 2 days prior to each planned discharge day after each dose (Days 6 or 7 or Days 34 or 35) will be kept in the isolation until PCR-diagnosis results confirm that no influenza virus is present in a tested clinical specimen for at least two consecutive days.

Any subject still exhibiting evidence of influenza virus shedding in a nasal swab on Days 6 or 7 or Days 34 or 35 post-administration with each dose might be placed on influenza antiviral (oseltamivir) treatment at the standard dose for treatment of 75 milligrams (mg) twice a day for a course of 5 days.

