| Record local and systemic reactions                                                                                              |                                | X                                                                          | X  | X  | X  | X  | X  | X  | X    |           | X        | X                | X    |            |     |
| Instruct participant on use of diary card                                                                                        |                                |                                                                            |    |    |    |    |    |    | X    |           |          |                  | X    |            |     |
| Participant records unsolicited AEs                                                                                              |                                |                                                                            |    |    |    |    |    |    | X    | X         | X        |                  | X    | X          | X   |
| Possible oseltamivir antiviral treatment                                                                                  |                                |                                                                            |    |    |    |    |    |    | X*** |           |          |                  | X*** |            |     |
| Contingency to remain in isolation if nasal swabs (Day 6, 7, 34, or 35) are not free of influenza A virus                 |                                |                                                                            |    |    |    |    |    |    |      | X         |          |                  |      | X          |     |
| Discharge from isolation unit                                                                                                    |                                |                                                                            |    |    |    |    |    |    | X    |           |          |                  | X    |            |     |
| Review interim adverse events****                                                                                                |                                |                                                                            |    |    |    |    |    |    |      |           | X        |                  |      |            | X   |

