| Report SAEs                                                                                                                      |                                | X                                                                          | X  | X  | X  | X  | X  | X  | X    | X         | X        | X                | X    | X          | X   |
| Subject completion of study                                                                                                      |                                |                                                                            |    |    |    |    |    |    |      |           |          |                  |      |            | X   |

\*Some screening activities will be repeated on D28. All D0 to D7 activities will be identically repeated from D28 to D35.

\*\*Nasal swab collection will continue for each day subject remains in isolation after planned discharge day. Planned discharge day is D7 post-dose one and D35 post-dose two.

\*\*\*For subjects with evidence of viral shedding in nasal swabs during the final two days of each stay in the isolation unit (D6 or D7 post-dose one and D34 or D35 post-dose two).

\*\*\*\*Safety Monitoring Committee review on or soon after Days 8 and 36 for each sub-cohort.

---

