### **3.2.2 Secondary Outcome Measures**

Immune responses will be parameterized as the proportion of subjects with at least a four-fold rise after each dose from baseline or as the mean titer after each dose in any of the following:

- Serum hemagglutination inhibition (HAI) antibodies
- Serum neutralizing antibodies
- Serum immunoglobulin class A (IgA) or immunoglobulin class G (IgG) antibodies measured by enzyme-linked immunoassay (EIA)
- Mucosal IgA antibodies in nasal wick specimen

Virus shedding will be parameterized as the proportion of subjects shedding virus [detected by real-time reverse transcriptase polymerase chain reaction (rRT-PCR) in nasal or conjunctival swabs or by isolation in chicken embryos] at any time-point. Shedding data will be reported for every subject at every measured time-point. Molecular characterization of any isolated shed virus will be reported with sequence details of any loss of attenuation mutations.

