Subject screening for eligibility will continue and be completed on the second screening day (S2). This second screening day will occur the same day as scheduled admission to the isolation unit and administration of study vaccine or placebo (Day 0). Women will undergo pregnancy tests using urine samples. All subjects will undergo an ear, nose and throat (ENT) examination. Fully eligible subjects will be admitted to the isolation unit. At that time, nasal swab, nasal wick, and blood specimens will be collected for virologic and immunological testing prior to administration of study vaccine or placebo. Blood and urine specimens will be again collected for routine biochemical and hematological blood tests and urinalysis by dipstick; these results will serve to define baseline status for subject prior to receipt of study vaccine or placebo but will not be used for screening purposes. Subjects will be unaware of which allocation, LAIV H7N3 or matched placebo, is received; study vaccine and placebo will be masked. Subjects will be carefully monitored for adverse reactions while in the isolation unit.

All subjects will remain in the isolation unit for at least 7 days after receipt of study vaccine or placebo. Nasal swabs will be collected daily while subjects are in isolation to test for presence of influenza virus shed in the nasal passage. Any subject exhibiting conjunctivitis will also have a conjunctival swab collected on the day of appearance of the sign. Any subject exhibiting influenza A virus shedding, as determined by real-time RT-PCR positivity on a nasal swab specimen, in the 2 days prior to each planned discharge day after each dose (Days 6 or 7 or Days 34 or 35) will be kept in the isolation until PCR-diagnosis results

confirm that no influenza virus is present in a tested clinical specimen for at least two consecutive days.

Any subject still exhibiting evidence of influenza virus shedding in a nasal swab on Days 6 or 7 or Days 34 or 35 post-administration with each dose might be placed on influenza antiviral (oseltamivir) treatment at the standard dose for treatment of 75 milligrams (mg) twice a day for a course of 5 days.

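### The protocol gives conflicting instructions on whether a conjunctival influenza A positive in the last two planned isolation days keeps a subject in the unit

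*Protocol*

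**What the plan says.** Section 8.2.2.1 limits nasal swabbing after the planned stay to subjects who are asked to remain "because a nasal (or conjunctival) swab specimen was influenza A positive during the final two planned days of stay in the isolation unit". A conjunctival positive is therefore named, in parentheses, as a ground for staying.

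The rules that decide who stays and who leaves are worded differently:

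- **Retention rule.** The Protocol Summary applies it to "Any subject exhibiting influenza A virus shedding, as determined by real-time RT-PCR positivity on a nasal swab specimen". Section 4 has the same test: "as determined by real-time RT-PCR positivity on a nasal swab specimen, in the 2 days prior to each planned discharge day after each dose".
- **Trial Scheme.** The relevant row reads "Contingency to remain in isolation if nasal swabs (Day 6, 7, 34, or 35) are not free of influenza A virus", and its footnote adds "Planned discharge day is D7 post-dose one and D35 post-dose two".
- **Result-holder check.** Sections 5.3.2 and 8.2.2.1 have one designated investigator receive all daily rRT-PCR results. On Days 7 and 35 that person is asked to confirm that no nasal swab from the last two days was positive.
- **Discharge.** Step 9 of sections 7.2.8 and 7.2.17 directs discharge once the two final nasal swabs are negative, with no condition on an eye swab.

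On conjunctival swabs, section 8.2.2.1 says: "Conjunctival swab specimens will be collected only on the first day of appearance of conjunctivitis". It gives them the limit it also gives nasal swabs from Days 1-6 and 29-34: "results (influenza A positive or negative) of testing for a subject must be complete and determinant within 30 hours of specimen collection". Section 3.2.2 counts a subject as shedding when virus is found by rRT-PCR "in nasal or conjunctival swabs or by isolation in chicken embryos".

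**The concern.** Isolation is the plan's containment measure for a live, avian-derived vaccine virus in phase I. A site needs one answer to whether a PCR-positive subject may leave. For a subject whose conjunctivitis first appears on Day 6, 7, 34 or 35, whose eye swab is positive and whose nasal swabs are negative, section 8.2.2.1 implies staying and step 9 implies leaving.

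The other safeguards do not settle it. Unit staff are blinded to PCR results. The result-holder is not blinded, but the question put to that person on Days 7 and 35 concerns nasal swabs only. Section 5.3.2 otherwise limits disclosure of a positive result to premature departure from the unit. The eye result may also not yet exist at the time of discharge.

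**Working it through.** The protocol states no figure on this point, so the check is a comparison of texts plus clock arithmetic.

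**1. The same subject under each rule** (eye swab positive on Day 6 or 7, nasal swabs negative on both days; the same applies to Days 34 and 35)

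| Place in protocol | Swab named | Consequence |
|---|---|---|
| 8.2.2.1, continued swabbing | nasal or conjunctival | presupposes the subject stays |
| Protocol Summary and section 4, retention rule | nasal | not triggered |
| Trial Scheme, contingency row | nasal | not triggered |
| 5.3.2 and 8.2.2.1, result-holder check | nasal | passes |
| 7.2.8 and 7.2.17, step 9 | nasal | discharge |
| 3.2.2, shedding outcome | nasal or conjunctival | counted as shedding |

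Four nasal-only rules, stated in 2 + 1 + 2 + 2 = 7 places, stand against one sentence that includes the eye. I found nothing that reconciles them.

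**2. Timing of the eye result.** Inputs: the 30-hour limit (8.2.2.1), planned discharge on Day 7 or 35 (Trial Scheme footnote), and Day 7 and Day 35 nasal results due by 16:00 (7.2.8 and 7.2.17, step 1). No discharge hour is given, so two are tried.

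Latest eye swab with a guaranteed result = discharge time - 30 h.

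- Discharge at the very end of Day 7: 24:00 Day 7 - 30 h = 18:00 Day 6.
- Discharge directly after the nasal deadline: 16:00 Day 7 - 30 h = 10:00 Day 6.
- Earliest possible Day 7 eye swab: 00:00 Day 7 + 30 h = 06:00 Day 8, already past the planned discharge day.

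So no Day 7 eye swab has a result guaranteed on the planned discharge day, whatever the hour. Adding 28 days gives the same for Days 34 to 36. Thirty hours is a ceiling: results may come sooner, but nothing requires it.

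**3. Exposure.** Planned discharges: 40 subjects x 2 doses = 80. Vaccine recipients: (9 + 21) x 2 = 60. These are upper bounds. The affected subset needs conjunctivitis first appearing on one of four study days, a positive eye swab and two negative nasal swabs. The protocol gives no rate for that combination.

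**The case against.** The strongest reply is that one parenthesis, in a sentence about when nasal swabbing continues, should not outweigh seven consistent nasal-only statements, and that deleting the parenthesis would also restore consistency. That deletion would work as an edit. It would, however, settle a containment question by letting out a subject whom the protocol's own outcome counts as shedding, and the sponsor should decide that openly.

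Two stronger readings are tempting, and the documents support neither.

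- **A reader might infer that the eye-only positive subject is in fact discharged.** The text gives two answers. Seven days is a minimum stay, section 8.2.2.1 contemplates the subject remaining, and the result-holder receives all rRT-PCR results and would know of any eye result already available. A site could retain the subject. What is shown is conflicting instruction, with discharge as the result of following step 9 literally.
- **A reader might infer that such a subject could never be released**, because section 4 asks for two consecutive days without virus and the eye is swabbed only once. Section 4 refers to a tested clinical specimen without saying that it must be from the eye. The later mention of both swab types under the virological assays describes what goes to PCR and does not define clearance. Follow-up in 8.2.2.1 and the Trial Scheme footnotes is by nasal swab, and the parallel clearance rule in 5.4.2.5 is nasal. Release after an eye positive is left unstated; it is not impossible.

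Two further points stand. The transmission warning in section 2.3.1.1 concerns virus replicating in the upper respiratory tract, and the protocol states no transmission risk from an eye-only positive. The outcome definition in 3.2.2 was not written as a containment criterion. Both keep the point minor.

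**Conclusion.** The point holds as an inconsistency in a containment rule. Section 8.2.2.1 treats a conjunctival positive on Days 6-7 or 34-35 as a reason to stay, while the retention, checking and discharge rules do not. An eye result from Day 7 or 35 is also not guaranteed before discharge.

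The number affected cannot be calculated. It is bounded by 80 discharges (60 in vaccine recipients) and expected to be small, given the conditions that must coincide. No primary or secondary estimate changes: a subject with an eye positive already counts as shedding, whether or not discharge follows. The conclusion rests on the wording alone. The timing part assumes only that discharge takes place on the planned day and that laboratories may use the full 30 hours. It is a minor containment-safety correction, worth making because it is cheap.

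**What to change.** - In the retention rule (Protocol Summary and section 4), the Trial Scheme, 5.3.2, 8.2.2.1, and step 9 of 7.2.8 and 7.2.17, add that any conjunctival swab collected on Days 6-7 or 34-35 must also be influenza A negative.
- Have the result-holder confirm this on Days 7 and 35.
- Test such swabs with the same-day nasal batch, or hold discharge until the result is available.
- State the release criterion for a subject kept on an eye positive. One workable form is negative nasal swabs on two consecutive days after the positive eye swab. A repeat eye swab can be optional; if it is allowed, the first-day-only limit needs an exception.

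**Cost.** This is mainly protocol wording. The eye swab is already collected, and section 8.2.3.3 sends nasal and conjunctival swabs to the same laboratory each day. With same-day nasal results assumed, an eye positive on Day 6 needs negative nasal swabs on Days 7 and 8 (8 - 7 = 1 extra day), and one on Day 7 needs Days 8 and 9 (9 - 7 = 2 extra days). Days 34 and 35 are the same. The downside is thus a rare extra day or two in isolation, plus an occasional wait for a pending eye result that proves negative.
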